## Abstract

**Introduction:**

Fracture misdiagnosis is a common diagnostic error in emergency departments (EDs) and minor injury units (MIUs), leading to poor patient outcomes, unnecessary treatments and significant healthcare costs. Artificial intelligence (AI)-assisted fracture detection tools are now available for use in radiology workflows; however, the impact of these technologies on patient outcomes, experiences and overall care pathways in the real-world clinical setting is limited.

**Methods and analysis:**

We will conduct a prospective cluster randomised cross-over trial over a 6-month period, assessing the impact of an AI-assisted fracture detection tool in EDs and MIUs across 4 healthcare Trusts in the UK. Patients aged over 2 years old undergoing a plain film radiography for a suspected fracture as part of routine clinical care will be eligible for study enrolment. The trial will deploy Radiobotics’ RBfracture, a CE-approved AI-assisted medical device software for fracture detection at each site for 6 months. Randomisation will be at a cluster-level; a site will be randomised to begin with ‘AI on’ or ‘AI off’ for a month, followed by alternating active status each month for the remaining 5 months. The primary outcome will evaluate the incidence of ‘inappropriate healthcare contacts’ among patients receiving imaging for suspected fractures. This composite metric encompasses inappropriate referrals to fracture clinics, repeated hospital attendances and subsequent follow-up communications regarding missed fractures. The rates of these measures will be compared in the ‘AI on’ versus ‘AI off’ stages. Secondary outcomes will include patient-reported outcomes, clinician surveys, a predefined health economic evaluation assessing cost-effectiveness and budget impact and the diagnostic performance of the algorithm.

**Ethics and dissemination:**

The study has received ethical approval from the South Central—Oxford Research Ethics Committee (Reference: 25/SC/0252, approval date: 23 October 2025), and subsequently from the Health Research Authority (IRAS 3 57 391-A). The results of this study will be presented at relevant scientific conferences and peer-reviewed publications will be disseminated on wider public forums such as traditional and social media.

**Registration details:**

This is an ongoing, actively recruiting trial (ISRCTN23087950). Recruitment began in January 2026 and will run for 6 months at each site, with per-patient follow-up of 30 days and subsequent data analysis. This manuscript describes protocol version 1.1. The full protocol and statistical analysis plan are available from the corresponding author on request and will be deposited on the study’s public repository (https://github.com/[name]/SAMURAI) prior to publication of results.

## Introduction

 Fracture misdiagnoses are the most common diagnostic errors in emergency departments (EDs), and the leading cause of successful legal claims related to ED care.^1
2^ In the UK, 1.8 million fractures occur annually with a lifetime prevalence nearing 40% and representing 5.1% of the £2.1 billion annual UK ED attendance costs.^3
4^

EDs are high-volume referrers of X-rays, with 2.1 million performed every year in England and estimates suggest that between 3.7% and 8.7% are subsequently interpreted incorrectly resulting in a missed fracture.^5–7^ Missed fractures can delay recovery, prolong pain and erode trust in healthcare providers, while incorrectly diagnosed fractures can lead to unnecessary treatments and hospital visits as well as discomfort and inconvenience for patients.^7^ Misdiagnoses increase National Health Service (NHS) costs due to requirements for additional staff, training, insurance and potential litigation.^7^ They can negatively impact clinical staff, causing stress and affecting team morale.^7^

Fractures can occur from infancy to old age and involve any bone. The diverse mechanisms of injury make diagnosis complex and reliant on dedicated imaging expertise.^8^ Yet in practice, the initial evaluation of radiographs for injured patients is often performed by non-specialist clinicians, such as resident doctors or nurse practitioners. These healthcare professionals work in busy and distracting environments, often with inconsistent senior oversight, particularly outside normal working hours or when working in remote services such as minor injury units (MIUs).^9
10^

The accuracy of radiographic interpretive skills varies between and within staff groups, as well as at different times of the day, suggesting that professional experience and working environment are influential factors for those on the clinical frontline.^11
12^ While immediate ‘hot’ reporting by specialist radiographers has previously shown a reduction in diagnostic errors and patients receiving incorrect referral, a shortage of specialist reporting staff makes this solution unfeasible for continuous delivery (24 hours, 7 days) in the NHS.^7
13
14^

Advances in computer vision have led to the development of a range of commercially available artificial intelligence (AI) algorithms designed and approved to assist in fracture detection from plain radiographical imaging, many of which are already in use in hospitals in the UK and globally.^10
15^ These algorithms automatically process radiographs and identify the presence or absence of a fracture, highlighting regions of interest by producing heat maps, boundary boxes or text indicators.^16^ In silico studies have shown high accuracy rates for these tools, suggesting they could potentially reduce misdiagnosed fractures and improve clinical speed and efficiency; however, there is little prospective evidence on their performance in real-world clinical settings.^17
18^ National Institute for Health and Care Excellence (NICE) recommendations outline that certain fracture detection tools demonstrate potential clinical effectiveness and cost-effectiveness for routine clinical use; however, further evidence is needed to justify long-term deployment and widespread funding.^19–23^

To evaluate the impact of introducing AI to assist clinicians in detecting fractures, and its subsequent impact on patients presenting to EDs and MIUs, clinical staff and the wider NHS, we will conduct a multicentre cluster randomised control trial, using a regulatory approved medical device software to assist clinicians in the detection of fractures.

This study aims to directly address a number of the evidence generation recommendations from the NICE EVA. We hypothesise that implementation of an AI fracture detection tool will improve the accuracy of fracture detection, reducing both false positive and negative interpretations compared with contemporaneous ED clinician radiograph interpretation in EDs and MIUs without AI assistance, and will hence reduce the number of unnecessary healthcare contacts such as patient recalls and unnecessary fracture clinic referrals.

### Primary objective

To evaluate whether implementation of an AI fracture detection tool reduces the proportion of patients having unnecessary NHS healthcare contacts resulting from incorrect diagnoses, that is, unnecessary specialist referral or recalls/reattendances.

### Secondary objectives

To assess:

Diagnostic performance of the AI tool fracture detection toolComparison of diagnostic performance of AI-assisted fracture detection against the final radiology report as the reference standard.Technical performance of the AI fracture detection toolFailure to process images.Turnaround time to provide AI output.Impact on clinician experienceED staff user experience and perceived need for senior supervision.Patient care experienceThe proportion of patients receiving inappropriate or omitted appropriate intervention.EQ-5D Health-Related Quality-of-Life QuestionnairesService provisionThe number of ED attendances due to missed fractures or the same injury.ED length of stay.Health economic impact of AI-assisted fracture detectionChanges in healthcare resource use (ED/MIU attendances, admissions, follow-up imaging, fracture clinic appointments).Cost-effectiveness and budget impact analysis, including quality-adjusted life-years (QALYs), incremental costs, and the overall budget impact of implementing the AI tool within NHS urgent and emergency care pathways.

## Methods and analysis

Systematic Assessment of the Medical Utility of Radiology and Diagnostic Artificial Intelligence (SAMURAI-Fracture) will be a prospective cluster randomised cross-over trial, assessing the impact of an AI fracture detection tool in EDs and MIUs in the UK.

All patients undergoing a plain film radiograph in an ED or associated MIU over a 6-month period for suspected fracture will be eligible for inclusion in the study. Patient identification will be through the routine registration process in EDs and MIUs, where suspected fracture cases are flagged for imaging on electronic patient record (EPR) systems. Clinical and outcome data will be extracted from each site’s EPR and Radiology Information System (RIS)/Picture Archiving and Communication System (PACS), including attendance records, radiology reports, and subsequent ED/fracture clinic activity. Records will be linked at the patient level using NHS number, MRN and X-ray accession number prior to pseudoanonymisation, with the linkage key retained separately from the research dataset by the local site team, as described in the Data de-identification and management section. Data quality will be monitored with a sample of extracted records validated against source EPR/PACS data at each site. Patient-reported outcomes (EQ-5D-5L and experience measures) will be collected via Microsoft Forms, administered to consenting patients within 30 days of their ED/MIU attendance. Patients will be excluded from the study if any of the following apply:

Patients under 2 years old.Skeletal survey conducted to assess for non-accidental injury.Skull, facial bone, dental and cervical spine plain film radiographs.Thoracolumbar spine plain film radiographs in patients under 18 years old.Patient has opted out of data sharing on the National Data Opt-Out.Patient completes the opt out form advertised on posters in the ED.

Figure 1 summarises the overall patient pathway from initial screening to follow-up.

**Figure 1 F1:**
[figure not shown]
An example output from Radiobotics’ RBfracture algorithm. AI, artificial intelligence; ED, emergency department; NHS, National Health Service; PACS, Picture Archiving and Communication System. EQ-5D: is a short, standardised questionnaire used to measure health-related quality of life.

The study uses routinely collected clinical data to evaluate a pathway-level intervention. As the intervention does not alter the clinician’s ultimate management decision or patient outcomes at the point of care, the clinical pathway remains unchanged. Accordingly, identification of eligible patients and collection of outcome data for both primary and secondary endpoints will be conducted under an opt-out consent model. Information about this approach will be communicated through prominently displayed materials in ED and MIU, as well as via the national NHS Data Opt-Out system (copies of these documents are included as online supplemental material).

In addition, a nested subgroup of approximately 30 patients per site will be recruited to complete a brief patient-reported outcome and experience measure (EQ-5D-5L). This subgroup will include patients treated during periods when the AI tool is active (ON) and a comparable group treated when the AI tool is inactive (OFF). Patients will be approached on arrival to the ED and invited to participate, with follow-up completion of the questionnaire at 30 days postattendance. Consent for participation will be documented within the EPR.

Furthermore, approximately 20 clinicians per site will be invited to participate in a qualitative survey assessing perceptions and experiences of AI within their clinical practice. This survey will be administered at both baseline and study completion. Consent information will be clearly presented within the introductory section of each online survey, and completion of the survey will constitute informed consent. Copies of all patient and clinician questionnaires are included in the online supplemental materials.

The four Trusts participating in this study, Oxford University Teaching Hospitals NHS Foundation Trust, Oxford Health NHS Foundation Trust, Royal Berkshire NHS Foundation Trust, and Buckinghamshire Healthcare NHS Trust, are part of a unified imaging network in the Thames Valley. They have been chosen based on their capacity to provide diverse patient populations, encompassing variation in socioeconomic status, geographical location, and ethnicity, as per the INCLUDE guidance, ensuring that results are generalisable to the wider UK population.

### AI software

The AI software used in this study is RBfracture (V.2.4; Radiobotics, Copenhagen, Denmark), a Class IIa CE-marked, AI-enabled medical device designed to support clinicians in the detection of fractures and joint dislocations on plain radiographs in patients aged over 2 years. The software is capable of identifying suspected fractures across the appendicular skeleton, ribs, and thoracolumbar spine, as well as detecting joint effusions (knee and elbow), lipohaemarthrosis of the knee, and periprosthetic fractures.

RBfracture processes plain radiographs and highlights regions of interest using bounding-box annotations to indicate areas suspicious for pathology. These outputs are intended to support, rather than replace, clinical judgement and do not constitute a definitive diagnosis. The AI-generated annotations are displayed alongside the original images within the standard PACS, allowing seamless integration into the existing clinical workflow without altering image review processes (figure 2). The software version will remain fixed throughout the study period.

**Figure 2 F2:**
[figure not shown]
The overall patient pathway from initial screening to follow-up. AI, artificial intelligence. PA: Posteroanterior

### Training and implementation

User training will be delivered in line with the manufacturer’s standard programme, including structured teaching sessions and provision of written guidance on the intended use of RBfracture.

Prior to site activation, clinical staff in ED and MIUs and Radiology will receive standardised training on the RBfracture workflow. This will include instruction on how AI outputs are presented within PACS, clarification of its role as an adjunctive decision-support tool, and its scope of application, including eligible anatomical regions and patient populations. The AI output will be presented as bounding-box overlays within the existing PACS viewer, ensuring no disruption to standard clinical workflows.

Radiobotics will deploy a version-locked instance of the software at each participating site for the duration of the trial. Any required security or infrastructure updates will be documented and communicated to the study team to clearly distinguish these from any changes to the underlying algorithm.

### Operational considerations and monitoring

In the event of software or network downtime, or where radiographs are not processed by the algorithm (eg, due to technical failure or cases falling outside the intended use), standard clinical care pathways will be followed. All such instances will be centrally logged as part of the study’s technical performance evaluation.

Adherence to the allocated intervention status (AI ON/OFF) and clinician interaction with the AI output will be monitored locally by site research teams, with additional oversight provided by PACS teams within each cluster. Any protocol deviations will be reported to the central study team.

### Comparator

The comparator arm will consist of usual clinical practice, defined as contemporaneous interpretation of radiographs in ED and MIU settings without AI-assisted support for suspected fractures.

### Reference standard

The acquired plain radiographs will be subsequently reviewed by a radiologist or reporting radiographer as part of the standard institutional care pathway, with the final verified report acting as the reference standard for comparison against the initial ED clinician’s diagnosis. Reflecting a pragmatic, real-world workflow implementation, formal radiology reporters will not be blinded to the AI algorithm outputs. Discrepant or uncertain cases will not undergo independent research adjudication, as the AI software is utilised strictly as a supportive diagnostic tool rather than an independent decision-maker. Instead, diagnostic or reporting discrepancies will be managed via the normal clinical pathway, with the ultimate decision to treat determined by the responsible treating clinician based on a comprehensive synthesis of the clinical and imaging assessments.

### Cluster randomisation

The randomisation sequence for each cluster’s initial AI activation status (AI-on or AI-off in month 1) will be generated by a member of the study team using online randomisation software. A restricted randomisation approach will ensure balance across the three clusters, requiring at least one cluster in each starting condition; allocations assigning all clusters to the same condition will be rejected, and the first valid sequence retained. The sequence will be generated centrally, with code, random seed, and output archived in the Trial Master File to ensure reproducibility and auditability. Allocation will be implemented by the trial statistician, and the core research team will inform all sites so that they can organise locally with their PACS/informatics teams, who will be responsible for activating or deactivating the AI software as appropriate in each changeover. Following initial assignment, each cluster will follow a fixed 6-month alternating schedule (ABABAB/BABABA; figure 3). Data analysis will be undertaken by a statistician who will be blinded as to whether the AI tool was activated or inactivated within a given month.

**Figure 3 F3:**
[figure not shown]
Example sequences of AI-activation following randomisation of clusters. AI, artificial intelligence.

This study will be divided into three clusters:

Cluster 1:Oxford University Hospitals NHS Foundation TrustJohn Radcliffe Hospital ED (level 1 ED).Horton General Hospital ED (level 1 ED).Oxford Health NHS Foundation TrustAbingdon and Witney MIUs (level 3 EDs).Cluster 2:Royal Berkshire NHS Foundation TrustRoyal Berkshire Hospital ED (level 1 ED).Henley and Townlands MIUs (level 3 ED).Cluster 3:Buckinghamshire Healthcare NHS TrustStoke Mandeville Hospital ED (level 1 ED).Stoke Mandeville MIU (level 3 ED).

Figure 3 illustrates example sequences of AI-activation following randomisation of clusters.

### Outcome measures

The primary outcome is a measure of the proportion of ‘unnecessary healthcare contacts’, a composite measure consisting of unnecessary NHS contact resulting from false negative diagnoses, for example, phone consultations, repeat ED attendance, and those resulting from false positive diagnoses, for example, fracture clinic attendance. This will be recorded as a binary outcome, that is, whether a patient has/has not had an unnecessary healthcare contact during the follow-up period following discharge.

Secondary outcome measures include technical performance of the algorithm, and its impact on service, clinical team, and the patient. Algorithm technical performance will include:

Measures of diagnostic performance metrics against the final diagnosis provided by the radiology report.Subgroup analysis by anatomical region, fracture type, patient demographics, and other existing pathology.Number of radiographs not processed by the algorithm that fall under its intended use.Patient-reported outcomes via the EQ5D questionnaire.

The major risk from this study includes the calling of false negatives, and false positives from the AI tool. In such cases, clinicians can report specific cases of failures to the central study team. Interim analysis will identify any increases in the false negative rate over the ‘AI-on’ period. Additionally, there is a risk of over-reliance on the tool or errors in interpretation. Clinicians will be reminded to use the AI outputs as an adjunct to their clinical judgement, rather than replacing it. There is a risk of automation bias among clinicians utilising the AI tool, however all radiographs will undergo subsequent interpretation and reporting by a radiologist, reporting radiographer or other trained reporter, with relevant safety-netting protocols in place.

### Statistical analysis

The data analysis plan has been formulated. The study design is a multiperiod treatment crossover design where treatment (the use of an AI tool) is applied sequentially over time to each site. This design has been employed to ensure a balanced distribution of AI on and AI off periods across all sites including longitudinally throughout the progress of the study to minimise the effects of any seasonal variation in injury patterns. Because the real-time presentation of AI bounding boxes may alter baseline clinician interpretive habits, diagnostic modifications could theoretically persist into subsequent control blocks (a learning or carry-over effect). To isolate and control for this potential operational bias, the primary statistical model incorporates an explicit time-dependent carry-over effect term. Within-cluster estimators will separate the direct treatment effects of active AI support from residual behavioural learning shifts across sequential monthly periods. As treatment in one period may affect the response during that period and during a later period (a carryover effect), the comparison between periods with and without the intervention can be biased. To account for any potential bias, we will use a statistical model that allows for within-subject estimators of the carryover and direct treatment effects. A linear model will be used for continuous outcomes and generalised linear models for skewed or categorical outcomes, and survival models where the outcome is time-to-event. Each model will have terms for site, period, treatment and carry-over effects. The level of statistical significance to be used in this study will be α=0.05. Subgroup analyses will explore impact of setting, algorithm, fracture type and age group.

The sample size was calculated to detect an absolute difference of 1.5% in the number of inappropriate NHS contacts. We anticipate an average of 3000 skeletal radiographs for possible fracture per calendar month per Trust. Of these, on average 800 per site are anticipated to show a fracture. Assuming a baseline inappropriate NHS healthcare contact rate of 5.5% (derived from historical data evaluating fracture pathway structural adjustments), a two-sided significance level of 5% is sufficient to detect an absolute reduction to 4.0% in the primary composite outcome of inappropriate healthcare contacts at ~80% power.^24^ Overall, the study will aim to recruit 45 000 patients across all sites. Patient impact will be measured by the total number of cumulative inappropriate contacts made (ie, fracture clinic referrals for false positives, Accidentes & Emergency (A&E) reattendances for false negatives), and patient-reported outcome measures (PROMs) for overall experience of care. Impact on clinician experience of care delivery will be assessed by questionnaire. AI impact on service delivery will be measured by comparing the number of correct and incorrect fracture clinic referrals, fracture related admissions, ED recalls due to missed fractures, ED reattendances and length of stay.

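### Strict monthly ON/OFF alternation leaves the direct AI effect and a previous-month carry-over effect inseparable after month 1, so the separation claimed for the primary model is not supported by the design

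*Protocol article*

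**What the plan says.** Under Cluster randomisation, the Protocol article states that after the initial assignment "each cluster will follow a fixed 6-month alternating schedule (ABABAB/BABABA; figure 3"). The same section says "This study will be divided into three clusters", with restricted randomisation "requiring at least one cluster in each starting condition". The start is therefore always two clusters against one.

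Under Statistical analysis, "the primary statistical model incorporates an explicit time-dependent carry-over effect term". The purpose is given as follows: "Within-cluster estimators will separate the direct treatment effects of active AI support from residual behavioural learning shifts across sequential monthly periods". The model terms are then fixed for all outcomes: "Each model will have terms for site, period, treatment and carry-over effects". The article gives no lag order or coding for the carry-over term, and does not say whether period is categorical or linear.

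The sample size paragraph takes a "baseline inappropriate NHS healthcare contact rate of 5.5"%, a reduction to 4.0%, a two-sided 5% level, about 80% power and 45,000 patients. It mentions no inflation for the carry-over term or for clustering.

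**The concern.** To separate a direct effect from a carry-over effect, a multiperiod crossover needs months with the same current status but different histories: ON after ON beside ON after OFF, and OFF after OFF beside OFF after ON. Strict alternation never produces ON after ON or OFF after OFF. Only month 1, which has no history, breaks the pattern.

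The primary estimate is at stake. If the stated model is fitted with a lag-1 term, most of the information in months 2–6 goes into a difference of two parameters, and the direct effect leans on the first month of use. If the term is coded as cumulative exposure, the model cannot be fitted. A coding chosen, or a term dropped, after seeing a wide interval or a singular fit would be a data-driven change to the primary model.

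**Working it through.** **The plan's own figure.** For 5.5% versus 4.0%, two-sided 5%, 80% power and pooled variance:

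n per arm = [1.960·√(2·0.0475·0.9525) + 0.8416·√(0.055·0.945 + 0.04·0.96)]² / 0.015² = 3,156, or 6,312 in total.

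With 45,000 patients (22,500 per arm) the power is above 99.99%. About 80% at 45,000 therefore does not follow from the stated inputs alone; the implied inflation is 45,000/6,312 = 7.13.

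**Aliasing.** Let T be the current month's status and L the previous month's (0 in month 1).

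| Month | 1 | 2 | 3 | 4 | 5 | 6 |
|---|---|---|---|---|---|---|
| ON-first: T / L | 1/0 | 0/1 | 1/0 | 0/1 | 1/0 | 0/1 |
| OFF-first: T / L | 0/0 | 1/0 | 0/1 | 1/0 | 0/1 | 1/0 |

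From month 2, L = 1 − T in every cluster, so τT + λL = λ + (τ − λ)T. Those months estimate only τ − λ. With month 1 dropped, the design matrix has rank 8 for 9 columns and τ is not estimable.

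**Variance ratio (fixed site, categorical period, equal months, independent errors).** Period terms reduce the data to the ON-first minus OFF-first difference in each month. Site terms centre those differences over the six months.

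- d_T = (1, −1, 1, −1, 1, −1): mean 0, sum of squares 6.
- d_L = (0, 1, −1, 1, −1, 1): mean 1/6, centred sum of squares 5 − 1/6 = 29/6.
- Cross-product −5, so r² = 25/(6 × 29/6) = 25/29 and r = −0.928.
- Variance ratio = 1/(1 − 25/29) = 29/4 = 7.25; SE ratio √7.25 = 2.69.

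The ratio does not depend on the 2:1 or 1:2 split, and holds with unequal cluster weights (2:1:1, 1:2:1, 1:1:2).

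**Where the information sits.** With equal clusters and two starting ON, the weights for τ in month 1 are +0.5, +0.5 and −1.0. In later months they are 0.08 to 0.25 in absolute size. The squared weights sum to 1.5 for month 1 and 1.8125 overall, so month 1 supplies 1.5/1.8125 = 83% of the variance. Without the carry-over term the total is 0.25.

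**Precision and power at 45,000.** There are 18 cluster-months of 2,500 patients, and p(1 − p) at 4.75% is 0.04524.

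- Without the term: SE = √(0.25 × 0.04524/2,500) = 0.21 points; 1.5/0.21 is about 7, so power is above 99.9%.
- With lag-1: SE = √(1.8125 × 0.04524/2,500) = 0.57 points; 1.5/0.573 = 2.62, and Φ(2.62 − 1.96) is about 75%.

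Both use binomial variation only. Applying 7.25 to a simple 22,500-versus-22,500 comparison (SE 0.20 to 0.54) gives 79.3%.

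**Other codings**, same formula, categorical period:

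| Carry-over coding | Monthly difference d | Ratio |
|---|---|---|
| Geometric decay, 0.5 | 0, 1, −0.5, 0.75, −0.625, 0.6875 | 8.74 |
| Lag-1 | 0, 1, −1, 1, −1, 1 | 7.25 |
| Cumulative exposure, OFF months only | 0, 1, −1, 2, −2, 3 | 4.38 |
| Lag-1 × months since start | 0, 1, −2, 3, −4, 5 | 3.34 |
| Ever exposed (permanent) | 0, 1, 0, 0, 0, 0 | 1.25 |
| Cumulative exposure | 0, 1, 0, 1, 0, 1 | not estimable |

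In the last row, cumulative prior exposure equals (t − 1)/2 + S/2 − T/2, where t is the month and S marks an ON-first cluster. It is an exact combination of period, site and treatment, even with a linear period term. Refitting the lag-1 model with a linear or absent period term gives ratios of about 2.9 to 6.3 in equal clusters, depending on the allocation.

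**Cost of omitting the term.** The regression of d_L on d_T is −5/6, so the model without carry-over estimates τ − (5/6)λ. With τ = −1.5 points, λ = −0.3 gives −1.25 and λ = +0.3 gives −1.75.

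**The case against.** The strongest objection is that the article leaves the coding open, and a statistical analysis plan exists that is not shown. A lasting shift after first use is a fair reading of a learning effect, and under that coding the ratio is only 1.25. This stands as a limit on the size: 7.25 is conditional. It does not rescue the claim as stated, because separation then rests on assuming that learning never fades. Nor is this a detail left to the analysis plan. The article itself states what the primary model contains and what it will separate, and its own schedule defeats that for any effect of the previous month.

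A reader might infer that a real effect would probably be missed. The documents do not support this: with binomial variation only, power is still about 75%. A lower figure needs a cluster-period correlation, and the article gives none.

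A reader might also infer that 45,000 is too small because of carry-over alone. But 6,312 × 7.25 = 45,762, within 3% of 45,000. The article does not say that such an inflation was applied, and the match may be coincidence. If it was applied, nothing is left for cluster-period variation with three clusters.

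It would be too strong to say that the estimate is just the month 1 contrast. Later months serve as the within-site reference. The reference to within-subject estimators is only a matter of wording, since the same paragraph speaks of within-cluster estimators.

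Finally, dropping the term trades variance for bias, and the result is not always conservative. Under Outcome measures the article itself raises over-reliance and automation bias. If reliance on AI worsened unaided reading in OFF months, omission would exaggerate the benefit. This stands and has to be stated with the fix.

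**Conclusion.** The concern holds in a conditional form. Under the fixed alternating schedule, months 2–6 identify only the direct effect minus any lag-1 carry-over, and without month 1 the two are inseparable. The stated separation is not a property of this design.

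The 7.25-fold variance and the fall in binomial-only power to about 75% assume fixed site, categorical period, lag-1 carry-over, equal months and independent errors; the standard errors and power also assume equal clusters. Across the codings examined with a categorical period, the ratio runs from 1.25 to 8.74, and cumulative exposure cannot be fitted. The size therefore depends on a choice that the article does not state. The model statement and the schedule must be reconciled before analysis, because the primary estimate and its precision depend on it.

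**What to change.** Before analysis:

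- Make the primary model site, period and treatment.
- Move carry-over to prespecified sensitivity analyses with the coding written out: the lag-1 model, exclusion of the first days after each switch, and the early versus late part of OFF months.
- Delete the statement that the model separates direct from residual effects.
- State that the primary estimate is the effect under monthly alternation. Add that leaving out carry-over shifts it by 5/6 of any lag-1 carry-over: toward the null if learning persists into OFF months, away from it if reliance on AI worsens unaided reading.

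This is a change of wording in the protocol and analysis plan. It needs no new data and no change to the schedule, which matters because recruitment is already under way. The price is the possible bias just described, in exchange for a direct-effect variance 7.25 times smaller than under the lag-1 model.
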